#### Change in adherence

The change in adherence will be determined by the mean of the level of adherence to the use of orthopedic shoes measured 6 months after inclusion minus the mean of the level of adherence to the use of orthopedic shoes measured 3 months after inclusion.

#### Total wearing time

The total wearing time of the orthopedic shoes during the 12-month follow-up will be based on log data from temperature microsensors in the orthopedic shoes of all participants and will be analyzed for different periods.

#### Complications

The proportion of participants (re-)experiencing complications (i.e., one or more ulcers or abundant callus that requires debridement, not present at baseline, or lower-extremity amputation) will be determined by the registration of (re-)experienced complications after receiving their orthopedic shoes, up to 1 year after baseline. All complications will be registered and photographed by podiatrists, who are informed by the participant if complications occur (in > 95% of complications cases, the podiatrist is the first to hear from the participants). If it is necessary to obtain details on specific complications, general practitioners or orthopedic surgeons will be contacted. Photographs will be assessed by observers blinded to treatment allocation to confirm the type and/or severity of the complication.

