#### Time point “− T1”—inclusion

After referral of the podiatrist, the pedorthist and medical specialist will decide together, during a multidisciplinary consultation, which type of shoes the patient will need. When instead of custom-made orthopedic shoes convection shoes or semi-orthopedic shoes will be prescribed, the patient cannot be included in the study. After the patient has been prescribed custom-made orthopedic shoes, he/she will be asked if he/she decided to participate in this study, and the investigator or the investigator’s representative will ask the patient to sign informed consent. Also, the demographic data (age, gender, ethnicity, height, and weight), diabetes type and duration, risk profile, ambulatory status, history regarding the use of orthopedic shoes, educational status, socioeconomic status, and capacity for self-care are completed. Subsequently, data on the presence of peripheral artery disease, peripheral neuropathy, foot deformities, and history of previous foot ulceration and amputation will be recorded, and the participants will be asked to fill in specific questionnaires (time point “− T1” at Table 2).

Thereafter, during a consult with the pedorthist, the orthopedic shoes will be fitted. The pedorthist will provide the new digital shoe-fitting procedure or the casting-based procedure depending on whether the podiatrist is trained in MI or not.

Within 1 to 6 weeks, the participant from the intervention group will have another consultation with the MI-trained podiatrist (first consult: participant was referred to the pedorthist). The podiatrist will apply MI in this conversation. From all included participants, thirty participants, 15 from both groups, will be approached for an in-depth interview about their perspective on and experiences with orthopedic shoes before receiving these shoes. This interview will be performed by one of the investigators.

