#### Time point “T0”—receiving the first pair of orthopedic shoes (baseline)

Two to 3 months after the multidisciplinary consultation, the participant will receive their first pair of orthopedic shoes during a consultation with the pedorthist. A temperature microsensor (Orthotimer®) is embedded in the insole of the orthopedic shoes for determining adherence by measuring and recording wearing time.

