Second, due to this new role of the pedorthist, the background assignment of the treating podiatrist (being trained in MI or not) no longer determines the shoe-fitting procedure by the pedorthist. Each pedorthist has his/her own procedure of shoe-fitting: the new digital shoe-fitting procedure or the casting-based shoe-fitting procedure. In addition, the existing last is also used for an extra pair of orthopedic shoes, and thereby the shoe-fitting procedure is already determined for each subsequent pair of orthopedic shoes. However, the background assignment of the treating podiatrist remains leading over the shoe-fitting procedure with regard to which group the participant belongs to (intervention or control group), because most participants have been treated by the same podiatrist for years and we do not want to change that for this study. The participants in the intervention group will have an appointment with their podiatrist or one of the other MI-trained podiatrists to perform motivational interviewing before or as soon as possible after they receive their first or new pair of orthopedic shoes.

Last, the second group of 12 additional podiatrists received MI training, and 16 podiatrists have been added to the control group to further increase inclusion. Because the inclusion in the intervention group lagged behind the control group, the second group of podiatrists, who received MI training, consists of the podiatrists who see most patients with diabetes. This is in contrast to the original group of podiatrists, who were assigned to one of the groups based on stratified randomization.

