In addition, a few small changes to the number of study consultations have also been made: 1) We reduced the number of six consultations that the participants would have with one of the investigators by two consultations. The investigator sees the participant at the delivery of the orthopedic shoes (T0), and 3 months (T1), 6 months (T2), 9 months (T3), and 12 months (T4) after the participant received their orthopedic shoes. 2) As a result of this change, the participants will receive the activity monitor during T1 (3 months) and T2 (6 months) instead of T1 (2 to 4 weeks) and T3 (4 months) as shown in Table 2. 3) All participants will be asked to fill in the MOS 6 months after receiving their orthopedic shoes, also the participants who will be approached for a second in-depth interview. 4) During every consultation with one of the investigators, the participant will be asked if they have an ulcer or have had an ulcer in the last 3 months. If so, the participant will be asked to fill in the iPCQ.

In conclusion, this trial aims to assess the (cost-)effectiveness of this novel care approach compared to usual care in terms of adherence to orthopedic shoes and ulcer prevention. The outcomes of this trial will generate insights into the socio-economic impact of the novel care approach on adherence to orthopedic shoes. These are crucial steps toward better ulcer prevention in high-risk diabetes patients.

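### Detection of complications, mainly callus needing debridement, may differ by arm: unblinded podiatrists register the events, and only the intervention arm has an added podiatrist consultation

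*Protocol article*

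**What the plan says.** The Complications section defines the event as "one or more ulcers or abundant callus that requires debridement, not present at baseline, or lower-extremity amputation", counted from receipt of the shoes up to 1 year after baseline. On ascertainment it says: "All complications will be registered and photographed by podiatrists, who are informed by the participant if complications occur". In support it adds that "in > 95% of complications cases, the podiatrist is the first to hear from the participants". It also provides a check: "Photographs will be assessed by observers blinded to treatment allocation to confirm the type and/or severity of the complication". Section {17a} states that podiatrists cannot be blinded.

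Contact with podiatrists is not the same in the two arms. In the inclusion section, within 1 to 6 weeks, "the participant from the intervention group will have another consultation with the MI-trained podiatrist". The Discussion revises the timing: intervention participants have an appointment "to perform motivational interviewing before or as soon as possible after they receive their first or new pair of orthopedic shoes". Regular podiatrist visits at about 6 months (most participants) and 1 year (every participant) are not restricted to one arm.

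A second route exists. The Participant timeline section has the investigator ask about complications at every study consultation. Among the later changes, the Discussion words the question this way: "the participant will be asked if they have an ulcer or have had an ulcer in the last 3 months". The stated consequence of a positive answer is completion of the iPCQ.

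Baseline is shoe delivery, when "the participant will receive their first pair of orthopedic shoes during a consultation with the pedorthist". Under the revised schedule the investigator also sees the participant then.

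**The concern.** Three features combine. First, the person who decides whether an event enters the record knows the arm, and for callus the need for debridement is that person's own judgement. Second, the intervention arm has one more contact with that person, possibly during follow-up. Motivational interviewing is also meant to build a working alliance with the podiatrist (Background), so the treatment itself may change what participants report. Third, callus counts only if absent at baseline, yet previous callus is permitted at entry and the text describes no uniform foot check at T0 in both arms.

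Ulcer prevention is part of the stated aim, and the complication proportion is to be compared between arms with a generalized linear mixed model. If detection differs, that comparison mixes incidence with detection, and no model can restore events that were never recorded.

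**Working it through.** **Passages side by side**

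| Step | What the article provides | What it leaves open |
|---|---|---|
| Event reaches the record | Participant tells the podiatrist, who registers and photographs it | Registrar unblinded; reporting may depend on arm |
| Added podiatrist contact | Intervention arm only | Original plan: 1 to 6 weeks after inclusion, so before T0 at 2 to 3 months. Revised plan: before or after delivery |
| Regular podiatrist visits | About 6 and 12 months, no arm restriction | Do not offset the added contact |
| Blinded photograph reading | Confirms type and/or severity | Sees only what was registered and photographed |
| Investigator's question | Both arms, every study visit | Revised wording covers ulcers only and leads to the iPCQ; no stated path to the complication count |
| Baseline status of callus | Must be absent at baseline | No T0 foot check in the text; Table 2 could not be read here and should be checked |

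The figure above 95% concerns who hears first once an event is reported. It is not split by arm and does not give the share of events that are reported.

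**Size**

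The article gives no expected complication rate and no detection probability, so it has no figure of its own to reproduce. The sample-size calculation concerns adherence only. What follows is an illustration; the true rates and detection probabilities are assumptions.

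- Observed rate = true rate × detection probability. Write a for control and b for intervention.
- 110 per arm; design effect 1 + (11 − 1) × 0.01 = 1.10. This uses 220/20 = 11 participants per podiatrist and the intraclass correlation of 0.01 from the sample-size section, both set for the original 20 podiatrists and for adherence.
- SE = √{[a(1 − a) + b(1 − b)]/110 × 1.10}; x = (b − a)/SE.
- Two-sided rejection probability with no true difference = 1 − Φ(1.96 − x) + Φ(−1.96 − x).

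Example: true rate 30% in both arms, detection 85% in control and 95% in intervention.
- a = 0.30 × 0.85 = 0.255; b = 0.30 × 0.95 = 0.285; difference 3 points.
- SE = √(0.39375/110 × 1.10) = 0.0627; x = 0.478.
- Rejection probability = 1 − Φ(1.482) + Φ(−2.438) = 0.077.

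Spurious difference in points, then rejection probability:

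| True rate, both arms | Detection 85% v 95% | 80% v 95% | 75% v 95% |
|---|---|---|---|
| 20% | 2.0; 0.066 | 3.0; 0.086 | 4.0; 0.117 |
| 30% | 3.0; 0.077 | 4.5; 0.112 | 6.0; 0.164 |
| 40% | 4.0; 0.091 | 6.0; 0.145 | 8.0; 0.224 |
| 50% | 5.0; 0.110 | 7.5; 0.189 | 10.0; 0.301 |

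Equal detection (90% v 90%) gives no bias and 0.05.

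With a true benefit of 30% v 20%:
- Detection 85% in control and 95% in intervention gives 0.20 × 0.95 − 0.30 × 0.85 = −0.065, so −10 points shrinks to −6.5.
- Swapping the detection rates gives 0.20 × 0.85 − 0.30 × 0.95 = −0.115, so the benefit is exaggerated.

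**Direction**

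Extra detection after T0 would add events in the intervention arm. Callus seen before T0 could be recorded as already present, which removes later events, or be treated and then counted as new, which adds them. The net sign is open.

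**The case against.** Much of the case on the other side stands. Usual care is itself podiatrist foot care, and both arms have regular podiatrist visits, the last of them specifically to check the feet. The investigator's general question about complications covers both arms, and the later ulcer question may only replace the trigger for the iPCQ rather than withdraw the general one. Adverse events reported to or seen by the investigator are also logged. Blinded readers guard against misclassification of what is registered. In the original schedule the added consultation comes before T0, outside the counting window. Table 2 could not be read here, and an article condenses a fuller protocol.

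These points rule out several stronger readings that a reader might infer:

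- That complications count only when the podiatrist registers them. The investigator's enquiry is a second route; what is unstated is whether its answers are counted.
- That callus is trimmed at the added consultation while the same callus goes unseen in controls. The article describes a motivational conversation there, with no foot examination or debridement, and controls also see podiatrists.
- That the bias runs against the novel approach. The sign is open, as shown in the working.
- That costs are biased in the same way. Resource use comes from the iMCQ. The iPCQ goes to everyone at baseline and 12 months, and its event-triggered use now follows the investigator's question. None of these is said to need podiatrist registration.

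What remains is the unblinded registrar, the one-arm contact that may fall within follow-up, and the missing link from the investigator's answers to the complication count.

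**Conclusion.** The point holds as a risk: detection of complications may differ by arm, mainly for callus that needs debridement. The article does not show that it does differ. Neither direction nor size can be derived from it; the 2 to 10 points and rejection probabilities of 0.066 to 0.301 rest entirely on the assumed rates and detection gaps, including the choice of the intervention arm as the better detected one. The outcome is secondary and the primary adherence comparison is untouched. The change is worth making because it is cheap and uses visits already planned in both arms.

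**What to change.** Amend the Complications section and the list of small changes in the Discussion so that one ascertainment schedule applies to both arms at the existing investigator visits:

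1. At T0, note callus and ulcer status for every participant, as the reference for what was absent at baseline.
2. At 3, 6, 9 and 12 months, ask every participant the same scripted question on ulcer, callus debridement and amputation since the last visit.
3. Enter every positive answer directly in the complication register, whether or not the podiatrist registered it, and count it in the outcome. Routing it back through the podiatrist for registration would restore the unblinded gate.
4. Send all available photographs to the blinded readers.

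Do not exclude callus first recorded at the motivational interviewing consultation from the main analysis: that would delete events in one arm only. Use it at most as a sensitivity analysis, alongside one restricted to ulcers and amputations.

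The cost is a few minutes per visit and a short amendment. Recruitment began in July 2019, so ascertainment would change mid-trial. That must be reported, and participants already past T0 will lack the uniform baseline record. The investigators are not blinded either, so the gain comes from identical wording and timing, not from masking.

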#### Participant-perceived quality of life

The participant-perceived quality of life of participants will be assessed with the 5-Level EuroQol Quality of Life Scale (EQ-5D-5L) questionnaire [37] and RAND-36 item Health Survey V2.0 (RAND-36 V2.0) [38]. The negative impact of complications on quality of life will be based on the literature. Quality-adjusted life years (QALYs) will be calculated based on the quality of life calculated from the EQ-5D-5L and the time duration between measurements, or the time until the end of life, based on the Dutch tariff established for the EQ-5D-5L [39].

#### Experiences of participant

A mixed methods approach will be applied to obtain the participants’ experiences and perspectives regarding their knowledge about the aim of orthopedic shoes, their satisfaction with communication with the pedorthist regarding wearing orthopedic shoes, their intentions to change wearing behavior, and their satisfaction with orthopedic shoes. A quantitative questionnaire (Monitor Orthopedic Shoes post-part (MOS) [40]) will be used to measure participant experiences on orthopedic shoes, use, and usability at 6 and 12 months after baseline. The information from the MOS will be complemented with data from in-depth interviews with 30 participants at baseline and 6 months after baseline. Participants will be selected randomly for the interviews: 15 participants of the intervention group and 15 of the control group.

#### Experiences of podiatrist

A mixed methods approach will be applied to obtain the MI-trained podiatrist experiences, with quantitative analysis of observed application of MI by the MI-trained podiatrist scored with the Motivational Interviewing Treatment Integrity (MITI) [41] and with interview results. The in-depth interviews will be taken after the last participant had his/her last consultation with the podiatrist.

#### Application of motivational interviewing

Between 1 and 2 months after the MI training, all podiatrists (the MI-trained and the non-MI-trained) will audio record some conversations with the participants for the assessment of applying MI or not. A health psychologist, educated in training motivational interviewing by the MINT, will be responsible for scoring the quality of the MI applied by the podiatrist with the MITI. To explore whether there is, as expected, a difference between the MI-trained podiatrists and the non-MI-trained podiatrists in the application of MI principles, also conversations from the non-MI-trained podiatrists will be scored with the MITI.

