### Additional consent provisions for collection and use of participant data and biological specimens {26b}

On the informed consent form, participants will be asked if they agree to the storage and use of their personal information for future research on adherence to orthopedic shoes. By signing the informed consent form, participants give permission to inform their podiatrist and pedorthist about their participation in the study and inform them when there are unexpected findings that are or could be important to the health of the participant, record one of the consultations with their podiatrist, for the research team to request medical information from their medical files, and when necessary to share data with the competent authorities. Biological specimens will not be collected for this trial.

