### Assignment of interventions: blinding

#### Who will be blinded {17a}

Blinding and concealed treatment allocation for podiatrists is not feasible, because of the way of randomization (see the “Concealment mechanism {16b}” section). Outcome assessments and analyses are not performed by independent staff, but by the investigators themselves, and therefore, they are also not blinded to the treatment allocation (see the “Concealment mechanism {16b}” section).

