#### Data management {19}

As required by the funder (ZonMw), a data management plan has been developed for this study. The participants will be coded by the letter of the participating center (one letter) and the letter of intervention or control group (one letter) followed by the number of the participant (four digits). All personally identifiable information will be saved in a locked cupboard with the coordinating investigator and on a computer protected with a password. All data will be collected on paper and then entered electronically in an Excel database by the investigator. All pseudonymized study data will be entered in a specific server facility (LISA) of the University of Twente for storage and archiving. The handling of the data will comply with the EU General Data Protection Regulation and the Dutch Act on Implementation of the General Data Protection Regulation (Uitvoeringswet AVG, UAVG). All study information will be saved for 10 years after the study ends in DANS (Data Archiving and Network Services). Access to original data on paper will be kept in a locked cupboard at the university with the coordinating investigator during the study.

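### The comparison of MI application has no rule for which consultations are recorded and no masking of the MITI rater, so it is open to expectation bias and possibly selection bias (minor)

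*Protocol article*

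**What the plan says.** The difference in MI application between trained and untrained podiatrists is secondary objective 8 (Objectives {7}) and outcome 8 (Outcomes {12}).

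- **Recording.** In Application of motivational interviewing, all podiatrists in both groups "will audio record some conversations with the participants for the assessment of applying MI or not". Under the consent provisions {26b}, participants allow the team to "record one of the consultations with their podiatrist". Neither place says how many conversations are recorded per podiatrist, which ones, or who picks them.
- **Scoring.** One health psychologist with MINT education "will be responsible for scoring the quality of the MI applied by the podiatrist with the MITI". The purpose is given as: "To explore whether there is, as expected, a difference between the MI-trained podiatrists and the non-MI-trained podiatrists" in applying MI principles.
- **Knowledge of allocation.** Concealment mechanism {16b} states that allocation is not hidden from the podiatrists.
- **Blinding.** Who will be blinded {17a} says: "Outcome assessments and analyses are not performed by independent staff, but by the investigators themselves, and therefore, they are also not blinded".
- **Coding.** Under Data management {19}, the participant code contains a centre letter and then "the letter of intervention or control group (one letter) followed by the number of the participant (four digits").

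**The concern.** A MITI score is a judgement made from a recording. It can be distorted in two ways without any real difference in practice. A rater who knows who was trained, and expects a difference, may score accordingly. And if the recordings are not a fair sample of each podiatrist's consultations, the scores describe the sample and not usual practice. As written, the plan guards against neither.

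This matters because the MITI comparison is the only measure of MI delivery that the article describes in both groups. The podiatrist interviews cover MI-trained podiatrists only. After the changes reported in the Discussion, the podiatrist's MI status no longer determines the shoe-fitting procedure but still decides the participant's group. If the primary result is null, the MITI scores will help to separate an ineffective MI from an MI that was not delivered. Bias towards apparent delivery would blur that distinction.

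**Working it through.** The article gives no numerical figure for the MITI comparison, so there is nothing to reproduce. The check is mainly a comparison of sections.

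**1. Is a sampling rule stated?** No. The outcome section speaks only of some conversations, and the consent section of one consultation per participant. By contrast, Experiences of participant states random selection for the in-depth interviews.

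**2. Is the rater masked?** No masking is mentioned. By contrast, Complications states that the photographs are assessed by observers blinded to allocation. Section {17a} gives unblinded assessment as the general position and makes no exception for MITI scoring.

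**3. Could the group reach the rater through the files?** Yes, if the files carry the participant code, because that code includes the group letter. How the audio files are labelled is not stated.

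**4. Could masking work?** Largely. The rater needs only the audio. Content may reveal training, so masking would be incomplete.

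**5. How large could the effect be?** This cannot be derived from the documents. The following illustrations rest on assumed shifts, with no true difference, and on a two-sided 5% test that the article does not name for this contrast.

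- *Podiatrists after expansion.* The Discussion adds 12 MI-trained and 16 control podiatrists to the 20 in Sequence generation {16a}. Assuming a 10/10 split of the first 20, the groups are 10 + 12 = 22 and 10 + 16 = 26. With one mean score each, the SE of the difference in SD units is √(1/22 + 1/26) = 0.290.
  - Net shift 0.3 SD: 0.3/0.290 = 1.04 SE, P(|Z| > 1.96) ≈ 0.18.
  - Net shift 0.5 SD: 0.5/0.290 = 1.73 SE, P ≈ 0.41.
- *First 20 podiatrists only (10 v 10, t-test with 18 df, noncentrality = shift × √(10/2)).*

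| Assumed net shift (SD of podiatrist score) | Rejection rate |
|---|---|
| 0 | 5% |
| 0.25 | 8% |
| 0.5 | 19% |
| 0.85 | 44% |
| 1.16 | 69% |

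- *How selection alone could create a shift.* If one group handed in the best of m conversations and the other an unselected one, the expected shift is the mean of the largest of m standard normal values: about 0.56 (m = 2), 0.85 (m = 3) and 1.16 (m = 5) SD of between-conversation scores. These equal podiatrist-level SDs only if each podiatrist contributes one conversation.

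These figures show that moderate shifts would matter with so few podiatrists. They do not show that any shift occurs.

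**The case against.** The strongest reply is that several tempting conclusions go beyond the text.

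- *That podiatrists choose which conversations to record.* A reader might infer this, but the article says who records, not who selects. What stands is that no stated rule prevents such a choice.
- *That the psychologist is unmasked.* Section {17a} speaks of the investigators, and nothing says that the psychologist is one of them or holds the key. Nor does that section cover every assessment, since the photograph observers are blinded. What stands is that no masking is provided for and the general position is unblinded.
- *That an expected difference signals bias.* A check after a 3-day training naturally expects one. It shows only which way an expectation effect would run.
- *That MITI is the only evidence that the groups differed in what they received.* This is too strong. The novel approach also includes digital shoe-fitting, and interviews with MI-trained podiatrists cover adoption and implementation. MITI is only the sole MI-delivery measure described in both groups.
- *That false positives would be 18–41%.* This depends wholly on assumed shifts, an assumed 10/10 split and a test that the article does not name. Selection in both groups could partly cancel.

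It is also fair to say that a condensed article may leave recording details to the full protocol. That largely answers the sampling point taken alone. It answers the masking point less well, because the article does state a general position on blinding and makes no exception for this subjective score.

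**Conclusion.** The point holds in a limited form. The article fixes no rule for which conversations the allocation-aware podiatrists record and gives no masking of the MITI rater. It also describes outcome assessment as unblinded and puts the group in the participant code. The exploratory comparison under objective 8 is therefore open to rater-expectation bias and possibly to selection bias.

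The size is unknown, and neither bias has been shown to operate. The primary outcome comes from temperature sensors and activity monitors and does not use the MITI score, so its estimate is untouched; only its interpretation depends on this measure. The masking part carries the weight, and the sampling part is closer to missing detail. Severity is minor.

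**What to change.** 1. Before scoring, remove the group letter, podiatrist identity and training status from every audio file and assign random labels.
2. Have the same psychologist score the files in random order, mixed across groups.
3. State in Who will be blinded {17a} that MITI scoring is a masked exception, and refer to it in Application of motivational interviewing.
4. For recordings still to be made, use consecutive eligible consultations, or dates drawn by the research team.

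The cost is slight: some relabelling work and a short recording instruction, with the same rater and no extra recordings. Steps 1 and 2 can be applied to any recording not yet scored. Step 4 cannot repair recordings already made, which may be many, since recruitment began in July 2019 and the second group of podiatrists has already been trained. Masking will remain imperfect where the conversation itself reveals training.
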